## Abstract

**Background:**

With a steep increase in the number of instrumented spinal fusion procedures, there is a need for comparative data to develop evidence based treatment recommendations. Currently, the available data on cost and clinical effectiveness of the two most frequently performed surgeries for lumbar spondylolisthesis, transforaminal lumbar interbody fusion (TLIF) and posterior lumbar interbody fusion (PLIF), are not sufficient. Therefore, current guidelines do not advise which is the most appropriate surgical treatment strategy for these patients. Non-randomized studies comparing TLIF and PLIF moreover suggest that TLIF is associated with fewer complications, less blood loss, shorter surgical time and hospital duration. TLIF may therefore be more cost-effective. The results of this study will provide knowledge on short- and long-term clinical and economical effects of TLIF and PLIF procedures, which will lead to recommendations for treating patients with lumbar spondylolisthesis.

**Methods:**

Multicenter blinded Randomized Controlled Trial (RCT; blinding for the patient and statistician, not for the clinician and researcher). A total of 144 patients over 18 years old with symptomatic single level lumbar degenerative, isthmic or iatrogenic spondylolisthesis whom are candidates for LIF (lumbar interbody fusion) surgery through a posterior approach will be randomly allocated to TLIF or PLIF. The study will consist of three parts: 1) a clinical effectiveness study, 2) a cost-effectiveness study, and 3) a process evaluation.

The primary clinical outcome measures are: change in disability measured with Oswestry Disability Index (ODI) and change in quality adjusted life years (QALY) measured with EQ-5D-5L. Secondary clinical outcome measures are: Short Form (36) Health Survey (SF-36), VAS back pain, VAS leg pain, Hospital Anxiety Depression Scale (HADS), complications, productivity related costs (iPCQ) and medical costs (iMCQ). Measurements will be carried out at five fixed time points (pre-operatively and at 3, 6, 12 and 24 months).

**Discussion:**

It is hypothesized that TLIF, compared to PLIF, has similar clinical outcome or is possibly better in reducing disability. Moreover, direct medical costs are expected to be lower due to less surgical morbidity, shorter hospital stay and shorter surgical time. Indirect costs are assumed to be lower for TLIF as well, because we suspect less working days are lost. Currently, prospective data comparing clinical and cost-effectiveness of both techniques are not available. Therefore, in clinical practice both techniques are used and the choice for technique is greatly based on surgeon’s preference. The demand for spinal fusion surgery has risen steeply over the last 10 years and is expected to increase even further in the near future. As a result, the burden on society (and the working population) will increase. In case our hypothesis is confirmed, treatment guidelines will be adapted, and TLIF will be recommended as first choice surgical treatment of lumbar spondylolisthesis. Ultimately this will lead to reduction of (direct and indirect) costs and better clinical outcome for spondylolisthesis patients eligible for instrumented spinal surgery.

**Trial registration number:**

Netherlands Trial Registry, number 5722 (registration date March 30, 2016).

## Background

Neurogenic leg pain is a frequent complaint in the general population. This pain is can be caused by compression or stretch of nerve roots or cauda equina fibers (lumbar radiculopathy or neurogenic claudication respectively). Lumbar disc herniation and spinal canal stenosis are the classic and most common causes. An other cause of neurogenic leg pain is becoming more and more prevalent, namely lumbar spondylolisthesis [1]. If conservative treatment for neurogenic leg pain fails, surgical treatment can be considered. In case of lumbar disc herniation or spinal canal stenosis, decompression surgery is executed. In case of spondylolisthesis, decompression alone is not sufficient, and additional spinal fusion is recommended and common practice nowadays. In the US, between 1998 and 2008 the national bill for instrumented spinal fusion has increased 7.9-fold [2, 3]. This only will increase further in the next decades with an aging population.

A number of surgical techniques for spinal fusion are available. Of these, transforaminal lumbar interbody fusion (TLIF) and posterior lumbar interbody fusion (PLIF) are most frequently performed in the Netherlands. Both procedures consist of pedicle screw placement. In the TLIF procedure, this is followed by placement of one cage in the intervertebral space using a unilateral approach. The PLIF procedure consists of placement two identical cages bilaterally in the intervertebral space using a bilateral approach.

There are no strict indications for using either techniques, because a number of prospective studies have shown that both methods effectively reduce leg pain [3–7]. As a result, the choice of technique is greatly based on surgeon’s preference. Even though these techniques are assumed to be equal, nonrandomized studies and one small RCT comparing TLIF and PLIF suggest that TLIF is associated with fewer complications, less blood loss, shorter surgical time and hospital duration [8–10]. Our own retrospective data of 254 TLIF and PLIF patients confirm this, and additionally reveal that TLIF patients score better on different quality of life related outcome parameters (SF-36, ODI) compared to PLIF [11]. These findings have not been confirmed in a randomized controlled trial.

However, with a steep increase in the number of instrumented spinal fusion procedures there is a need for comparative data to develop evidence based treatment recommendations.

This study proposes to analyse in a high quality design (multicenter prospective randomized controlled trial) effectiveness and cost-effectiveness of the TLIF technique compared to PLIF technique for patients with leg pain caused by single level lumbar spondylolisthesis.

## Methods

This study consists of three parts, each with its own research question:I.Clinical effectiveness1) Is transforaminal lumbar interbody fusion (TLIF) effective in reducing disability in comparison to posterior lumbar interbody fusion (PLIF) in patients with single level lumbar spondylolisthesis?II.Cost-effectiveness2) Is transforaminal lumbar interbody fusion (TLIF) cost-effective in comparison to posterior lumbar interbody fusion (PLIF) in patients with single level lumbar spondylolisthesis from a societal perspective?III.Process evaluation3) What are the experiences and opinions of patients and professionals regarding TLIF?

### Design

A nation wide, prospective, multicenter, patient blinded, randomized controlled superiority trial. Patients will be randomized into one of two parallel groups (1) TLIF and (2) PLIF in a 1:1 ratio. The study inclusion period will be approximately 2 years, and the follow-up period 2 years (total study duration 4 years). Informed consent will be acquired from all participants. The study has been approved by the local institutional medical ethical committee (Medical Research Ethics Committee Zuyderland, METC 16-T-36) and has been registered with the Netherlands Trial Registry, part of the Dutch Cochrane Centre (number 5722).

### Study population

One hundred forty four eligible lumbar spondylolisthesis patients will be included in this study. Eligible are patients with:Indication for LIF (lumbar interbody fusion) surgery through a posterior approachClinical mono uni- or bilateral lumbar radiculopathy or intermittent neurogenic claudication caused by a single level isthmic, degenerative or iatrogenic spondylolisthesis grade I, II or III at level L3L4, L4L5 or L5S1.Single level spondylolisthesis with central or foraminal stenosis on MRI (or CT), of which the anatomical level is corresponding the clinical syndrome.Age over 18 years.Psychosocially, mentally, and physically able to fully comply with this study protocol.Written informed consent prior to this study.

Patients will be excluded of participation in this study when any of the following criteria are met:Previous radiotherapy at the intended surgical level.(Progressive) motor failure and/or anal sphincter disorders which urges instant intervention.Active infection.Immature bone (ongoing growth).Active malignancy.Pregnancy.Symptomatic osteoporosis.Contra-indications for anesthesia or surgery.Inadequate command of the Dutch language.

### Setting and recruitment

This is a cooperating project involving six Dutch hospitals (Maastricht University Medical Center - Maastricht, Zuyderland Medical Center - Heerlen, University Medical Center Groningen - Groningen, Radboud university medical center - Nijmegen, Canisius Wilhelmina Hospital - Nijmegen and Isala - Zwolle). These hospitals have been chosen because of their high volume of instrumented spine surgery and their familiarity with TLIF and PLIF. Patients referred to the outpatient clinic with an indication for LIF surgery are eligible to participate in the study, and will be referred by colleagues to the researchers.

Researchers will inform the patient verbally and in writing. When the patient is willing to participate (patients are allowed to use a cooling off period of one week) an informed consent form will be signed by the patient and the researcher, and patients will be allocated randomly to either the TLIF or PLIF group.

### Sample size calculation

The difference in ODI improvement is defined as primary endpoint and will be used for calculating sample size. An improvement of seven points is considered a minimal clinically important difference [12]. Based on own retrospective data, ODI improvement after TLIF was 17.5 points (35 %), and 9.5 points (19 %) after PLIF. The response within each subject group was normally distributed with standard deviation of 16. Assuming that a true difference between the experimental and control group-means is at least eight, we will need to study 64 experimental subjects and 64 control subjects to be able to reject the null hypothesis that the population means of the experimental and control groups are equal with probability (power) of 0,8. The Type I error probability associated with this test of this null hypothesis is 0,05. Based on a 10 % loss to follow-up, we intend to include 144 patients (72 patients per group).

### Randomization

Participants will be randomly assigned by the researcher to either the TLIF or PLIF group with an 1:1 allocation using a web based computer generated randomization schedule stratified by treatment hospital and type of spondylolisthesis by variable block algorithm with random blocks of four, six or eight.

Patients are kept blinded for the allocated treatment during the follow-up period of two years.

At the end of the follow-up the blind can be lifted upon the patient’s request. The statistician is blinded as well.

### Interventions

#### TLIF group

The patient undergoes standard surgical treatment of degenerative listhesis with central spinal canal stenosis, or of isthmic listhesis with foramen stenosis. All patients receive antibiotic prophylaxis according to local hospital protocol. After receiving antibiotic prophylaxis, the patient is brought under general anesthesia and positioned prone. A midline or paramedian posterior approach is performed, exposing the posterior lumbar elements including the facet joints. Poly-axial pedicle screws are placed bilaterally, using fluoroscopic guidance or navigation, depending on preference of the surgeon. In case of spinal canal stenosis, the central part of the spinal canal is decompressed by laminectomy. Unilateral exposure to the intervertebral disc is assured by total unilateral facetectomy, decompressing the descending and leaving roots. In the case of bilateral symptomatic leg pain, the side of the unilateral approach is free of choice for the surgeon. Unilateral facetectomy is performed to gain access to the intervertebral disc. Discectomy is performed. Endplate cartilage is prepared to provide a host bed of bleeding subchrondral bone for placement of the cage. The TLIF cage size is determined by a trial cage and fluoroscopy. The definitive cage is filled with autologous bone or allograft and is tamped into place. Its position is checked radiologically. After placement of the TLIF cage, the remainder of the disc space is filled with autologous bone, obtained from the decompression. A titanium rod interconnects the screws on each side. The spreader is removed and the wound is thoroughly irrigated and closed in several layers without suction drainage.

#### PLIF group

Pedicle screw placement and if necessary, laminectomy as in the TLIF group. Bilateral access to the intervertebral disc assured by resection of the pars articularis inferior and partial resection of the pars superior of the facet joint. Bilateral discectomy is performed. Subsequently, endplate cartilage is prepared to provide a host bed of bleeding subchrondral bone for placement of the cages. Determination of cage size by trail cages and fluoroscopy. Before placement of the definitive cages, the disc space is partially filled with autologous bone, obtained from decompression. The definitive cages are also filled with autologous bone or allograft and are tamped into place with fluoroscopic guidance. Their position is checked radiologically. A titanium rod interconnects the screws bilaterally. The wound is closed in the same matter as in the TLIF group.

The flow of patients through the study is summarized in Fig. 1.

**Fig. 1 Fig1:**
[figure not shown]
Study design flow chart

### Post-surgical care

Standardly there is no postoperative administration of IV antibiotics. Position of the implants will be checked by means of lumbar spine X-ray (anterior-posterior and lateral). Patients are encouraged to mobilise, initially with guidance of a physiotherapist, and resume daily activities as soon as possible. No additional physical therapy at home is advised.

### (Clinical) effectiveness

To assess the (clinical) effectiveness of both procedures, patients are asked to fill out web based questionnaires concerning Patient Related Outcome Measurements (PROMS) at five fixed time-points, namely preoperatively and 3, 6, 12 and 24 months postoperatively.

#### Primary outcomes

Change in disability measured using the Oswestry Disability Index (ODI) [13] and change in quality adjusted life years (QALY) assed with EQ-5D-5L [14].

#### Secondary outcomes

Quality of life will be further assed using the Short Form (36) Health Survey (SF-36) [15].

Pain will be measured using the Visual Analogue Scale (VAS) score for back pain and leg pain [16].

The degree/presence of preoperative anxiety and depression will be measured using the Hospital Anxiety Depression Scale (HADS) [17]. Societal costs will be measured retrospectively with the a Medical Cost Questionnaire (iMCQ) and the Productivity related Cost Questionnaire (iPCQ) [18].

Direct and indirect surgical complications including dural tear, postoperative infection, deep venous thrombosis, hematoma, hardware failure, neurological deficits, medical other complications as pneumonia or urinary tract infection will be registered.

#### Other study parameters

Sex, age, BMI, smoking habits, occurrence of diabetes, diagnosis, level, grade of spondylolisthesis, previous back surgery and ASA classification. Perioperative morbidity will be correlated to use of antibiotics, duration of surgery, intraoperative blood loss and duration of hospitalization.

#### Economic evaluation

The economic evaluation will assess cost-effectiveness (CEA) and cost-utility (CUA) from a societal and health care perspective. Costs will be related to change in disability measured with ODI and change in cost-effectiveness analysis and to changes in quality-adjusted life years (QALYs) with EQ-5D-5L in the cost-utility analysis. The analysis will be performed with a time horizon of two years.

Data are collected in web based CRFs (case report forms) and by means of questionnaires. Included costs consist of: 1. health care costs, 2. patient and family costs and 3. other costs. Healthcare costs are for example costs of surgical intervention (either TLIF or PLIF), hospital care (including costs for treating complications), medication, outpatient visits and resource use outside the hospital such as general practitioner visits and physical therapist visits. Among patient and family costs are travel costs, informal care and home care. Other costs are costs such as productivity losses due to absence from work. Information on these costs will be collected with a questionnaire designed for consumption of healthcare in the Dutch system (Medical Consumption Questionnaire - iMCQ) and a questionnaire designed for productivity costs in the Dutch system (Productivity Costs Questionnaire iPCQ). Both questionnaires have a recall period of 3 months and will be administered repeatedly at five fixed time points.

#### Process evaluation

To assess the experiences and opinions of patients and professionals with TLIF a process evaluation according to the framework provided by Saunders will be performed [19].

This framework consists of a stepwise approach in which important characteristics for the process-evaluation plan are identified along seven basic components, namely: fidelity (quality), dose delivered (completeness), dose received (exposure), dose received (satisfaction), reach (participation rate), recruitment and context.

For this process evaluation both qualitative and quantitative data will be collected. At the end of the study a short interview will be held with the principal investigator of every participating center, where the investigator can reflect on his/her experiences with the surgical techniques. A patient board is set up to ensure patient representation. Patients will be questioned using a semi-structured questionnaire covering the topics identified in the framework provided by Saunders et al. [19].

### Analysis

#### Clinical effectiveness

Data will be analysed according to the intention-to-treat principle. Difference in ODI change and EQ-5D-5L between baseline and subsequent measurements will be analysed using analysis of covariance (ANCOVA) to correct the effect of intervention as compared to controls for potential baseline differences and to gain precision in the effect estimates. In addition, we will use linear mixed models to analyse changes within the treatment groups as well as differences between the intervention and control group in the ODI and EQ-5D-5L over time.

Linear mixed models will also be used to analyse changes on secondary outcome measurements over time both within and between groups (Short Form (36) Health Survey, VAS back pain and leg pain and Hospital Anxiety Depression Scale (HADS)). Multivariable linear regression analysis will be performed to determine differences in change scores between the two groups at fixed time points.

Differences in the proportion of participants that report complications over the study period (up to 24 months), will be evaluated by means of logistic regression analysis.

All results will be presented as absolute mean differences with 95 % confidence intervals, or odds ratios with 95 % confidence intervals.

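### Randomisation is stratified by hospital and type of spondylolisthesis, but no described analysis names either factor as a model term; if they are prognostic and left out, a modest amount of precision is lost

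*Protocol article*

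**What the plan says.** The Randomization section describes a "randomization schedule stratified by treatment hospital and type of spondylolisthesis by variable block algorithm with random blocks of four, six or eight". Setting and recruitment gives the number of centres: "This is a cooperating project involving six Dutch hospitals". Study population lists three types, with symptoms "caused by a single level isthmic, degenerative or iatrogenic spondylolisthesis grade I, II or III". If all three types are strata levels, there are up to 6 × 3 = 18 strata.

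Under Analysis, Clinical effectiveness, ODI change and EQ-5D-5L are compared by ANCOVA, whose purpose is "to correct the effect of intervention as compared to controls for potential baseline differences and to gain precision in the effect estimates". The section then adds a second approach: "In addition, we will use linear mixed models to analyse changes within the treatment groups", which also covers differences between groups over time. Change scores have their own sentence: "Multivariable linear regression analysis will be performed to determine differences in change scores between the two groups at fixed time points". Complications go into a logistic regression. None of these models has a covariate list, and neither hospital nor type of spondylolisthesis is mentioned in connection with any of them.

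**The concern.** Stratified blocks force the arms to be similar within each hospital and type. If those factors predict outcome, the balance removes variation between strata from the treatment contrast. A model without the factors does not register this: it leaves that variation in the residual, and its standard error exceeds the real sampling variability of the estimate. The intervals are then wider than the design warrants and power is lost.

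The stated rationale makes the omission easy to carry through to the analysis. A rule aimed at baseline differences directs attention to variables that turn out imbalanced. Stratification factors are balanced by design, so such a rule would not naturally select them, although they are the factors that serve the section's second aim, precision. The Discussion names sample size as a limitation, chiefly for secondary outcomes, so precision matters here.

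**Working it through.** **Inputs.** From Sample size calculation: difference 8 points, SD 16, power 0.80, alpha 0.05, 64 per arm, 10% loss, 144 in total. From Randomization, Setting and recruitment, and Study population: two factors with 6 and 3 levels, blocks of 4, 6 or 8. Assumed, because the protocol does not give it: R², the share of ODI-change variance explained by the strata, taken from 0 to 0.20.

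**Step 1: the plan's own figure.** n per arm = 2 × 16² × (1.96 + 0.84)² / 8² ≈ 63 by the normal approximation. The t-test version gives 63.8, so 64. Then 64 / 0.9 = 71.1, so 72 per arm and 144 in total. The plan reproduces with a two-sided test (one-sided would give 50). It uses the unadjusted SD and takes no credit for covariates.

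**Step 2: formulas under perfect balance, 64 completers per arm.**
- Model standard error without strata: 16 × √(2/64) = 2.83.
- Standard error with strata: 2.83 × √(1 − R²).
- True type I error if strata are ignored: 2 × [1 − Φ(1.96 / √(1 − R²))].
- Power if ignored: Φ[(8 − 1.96 × 2.83) / (2.83 × √(1 − R²))].
- Power if adjusted: Φ[8 / (2.83 × √(1 − R²)) − 1.96].

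| Assumed R² | Adjusted SE | Type I error, ignored | Power, ignored | Power, adjusted |
|---|---|---|---|---|
| 0 | 2.83 | 5.0% | 80.7% | 80.7% |
| 0.05 | 2.76 | 4.4% | 81.4% | 82.7% |
| 0.10 | 2.68 | 3.9% | 82.0% | 84.6% |
| 0.20 | 2.53 | 2.8% | 83.4% | 88.5% |

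**Step 3: simulation with the planned blocks.** With 18 strata there are about 144 / 18 = 8 patients per stratum, so many blocks stay incomplete and balance is imperfect. The simulation used 128 completers, six hospitals of equal expected size, types split 45/45/10% (assumed), R² shared equally between the two factors, and 3,000 runs per setting. Adjustment was by main effects: 5 + 2 = 7 degrees of freedom.

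| Assumed R² | Strata ignored: mean model SE / true SD of estimate | Type I error, ignored / adjusted | Power, ignored / adjusted |
|---|---|---|---|
| 0 | 2.820 / 2.827 | 5.2% / 5.4% | 79.6% / 78.6% |
| 0.05 | 2.829 / 2.772 | 4.5% / 5.2% | 80.9% / 81.7% |
| 0.10 | 2.824 / 2.706 | 4.3% / 5.4% | 81.6% / 84.7% |
| 0.20 | 2.829 / 2.605 | 3.2% / 5.2% | 81.8% / 87.6% |

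The overstatement of the standard error is 2.829 / 2.772 = 1.02, 2.824 / 2.706 = 1.04 and 2.829 / 2.605 = 1.09. The power differences are 0.8, 3.1 and 5.8 points. At R² = 0, adjustment costs about 1 point in this run, which is close to simulation noise. Monte Carlo error is about 0.4 points for type I error and 0.7 points for power. Incomplete blocks make the test somewhat less conservative than the formulas suggest.

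**Step 4: the comparator.** Both tables set a strata-adjusted test against an unadjusted one, whereas the plan uses ANCOVA. If the baseline score already captures part of what the strata explain, the relevant R² is only the part beyond it. The protocol gives no figure for that.

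**The case against.** The strongest reply is that silence is not a decision. The section gives no covariate list, does not say adjustment stops at the baseline score, and excludes nothing. Other study parameters lists diagnosis among the recorded characteristics, so type of spondylolisthesis could be one of the baseline variables meant. An article condenses a fuller protocol, and a covariate list is often left to the SAP, which is not shown.

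Much of this stands, and it rules out three stronger readings:
- A reader might infer that the analysis adjusts only for baseline differences. The text does not say so.
- A reader might infer that the standard errors will be too large. That holds only if the factors are both omitted and prognostic, and the protocol shows neither.
- A reader might infer that the regressions of change scores leave out the baseline value. The protocol calls them multivariable, so they have covariates, and the baseline value may be one of them.

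The objection does not dispose of the point. The section is not silent on adjustment: it states a rationale and names four model families, and that rationale points away from factors balanced by design. An analyst working from this text could reasonably leave both factors out.

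**Conclusion.** The point holds as a modest issue of efficiency and specification. It is certain that allocation is stratified on two factors and that the analysis text names neither, and the mechanism is well established. The size of the loss is uncertain. For an assumed stratum R² of 0.05 to 0.20 it is about 2% to 9% on the standard error, a type I error of about 4.5% to 3.2%, and about 1 to 6 points of power. At R² = 0 there is no gain and a trivial loss of degrees of freedom. The figures rest on the assumed R² and split of types, and are relative to an unadjusted test; the gain beyond a baseline-adjusted ANCOVA depends on what the strata add to the baseline score.

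The error is conservative. It does not inflate false positives, and it does not call the 64 per arm or the total of 144 into question.

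**What to change.** State in the Clinical effectiveness analysis section, and carry into the SAP, that hospital and type of spondylolisthesis enter the ANCOVA, the linear mixed models and the linear regressions as main effects, alongside the baseline value of the outcome. Main effects use 7 degrees of freedom; fitting up to 18 separate cells of about 8 patients would be wasteful.

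For complications, where events may be sparse, use a lighter adjustment: type of spondylolisthesis only, or a stratified (Mantel-Haenszel) estimate.

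The cost is one or two sentences. Both factors are already known for every patient at randomisation, so no new data are needed and the sample size does not change. Fixing the terms in advance also removes discretion over which baseline differences are corrected for.
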